### Therapist Training and Fidelity

Therapists for the study are trained on delivering both the *in vivo* and standard smoking cessation counseling protocols by the principal investigator of the study. The one-day training session includes reviewing the importance of smoking cessation, behavioral strategies for quitting, etc. The manual is highly structured to facilitate adherence to the intervention. When counselors covered the topics with at least 90% accuracy during practice, they were able to take study patients on their own. However, if they did not reach the 90% mark, they underwent further training and practice. While it is impossible to blind the intervening therapists to the current behavioral treatment they are delivering, the intervening therapist does not complete the follow-up sessions for the participants they treat. The follow-up assessor remains blind to the intervention delivered to participants. In addition, since most participants are able to complete the measures independently on a surface pro tablet or remotely through REDCap, no opportunity is present for the therapist to influence self-reported changes.

Sessions 1 through 4 are audio recorded by study staff for fidelity checks and 20% of all recordings are reviewed using fidelity worksheets to assess the session therapist adherence to the session. The other staff members trained in the intervention complete the fidelity worksheets for each other, so that no one completes them for sessions they conduct themselves. On each worksheet, there are specified topics that the therapist covers based on the therapist manuals. The reviewer indicates (yes/no) on the worksheet whether the therapist covered the session topics while listening to the audio recording for the session. Staff were trained by the PI using the worksheet to ensure coverage of specific items and topics. Therapists are required to score 90% or higher on the session otherwise they undergo additional training on the counseling interventions. Supervision was given during weekly meetings with staff and the principal investigator.

### Follow-Up Procedures

Following the four sessions for both groups, participants complete six brief check-ins to confirm their contact information (weeks 6, 10, 14, 20, 28, and 32) and five follow-up visits (weeks 8 and 12, months 1, 3, and 6), as shown in Figure 1. At each follow-up visit, participants complete questionnaires sent through an email/text link or over the phone with study staff. The participant also provides a carbon monoxide reading.

**Figure 1 F1:**
[figure not shown]
Study flow chart.

Prior to social distancing measures due to the COVID pandemic, CO was tested at all visits using the Vitalograph CO monitor. After start of COVID distancing measures, participants began being tested at baseline using both the Vitalograph CO monitor and the iCO Smokerlyzer monitor and then are given the iCO to use remotely. The Covita iCO Smokerlyzer is an individual CO monitor that connects to the participant's phone *via* the headphone jack and utilizes a phone application (iCO Smokerlyzer) to measure the participant's CO. The application instructs the participant how to complete the CO testing, asks them how many cigarettes per day (CPD) they are smoking, along with how soon they start smoking after waking up, and provides feedback to the participant about their CO level (e.g., Heavy smoker, Moderate smoker, etc.). Participants share their CO reading results with study staff *via* email directly from the iCO app, which allows study staff to continue to remotely verify smoking status in participants.

At weeks 8 and 12, participants are given instructions and reminders about the remaining NRT (4-week supply at both time points) and are reminded to track their tobacco and NRT use with study calendars until the Month 1 follow-up. At all follow-up visits until Month 6, study staff also verbally confirm pregnancy status for individuals who could become pregnant.

### Outcomes

The primary outcome variable will be smoking 7-day point prevalence abstinence confirmed by a CO ≤ 3ppm (if measured using the Vitalograph) or CO <6 ppm [if measured using the iCO Smokerlyzer; (55, 56)] at the 6-month follow-up. We will also examine abstinence across the study using the same CO-verified self-reported 7-day point prevalence abstinence. A secondary outcome includes medication adherence (defined as using >80% of doses) during the 10-week intervention period between groups. Adherence is assessed by self-report using timeline followback (TLFB) methods and prior to COVID, included verification through returned patches and blister packs of lozenges. Additional outcomes of interest include quitting across time and incidence, frequency, and duration of quit attempts. If participants are using other tobacco products, this will be reflected in the tobacco-use survey used to determine 7-day point prevalence abstinence for all products (e.g., e-cigarettes, cigars, chew/dip, etc.) as well as in the CO data for products that increase expired CO. In addition, this will be regarded as continued tobacco use and not as quit. Similarly, if participants are smoking other substances (e.g., cannabis) and are over the CO cutoff, regardless of self-report, they will be considered as smoking as we cannot separate the source of smoke through CO at follow-up. This is more conservative but given the high rates of comorbid tobacco and other drug use, particularly cannabis, it is unlikely they would stop one smoking behavior but continue the other.

### Sample Size Considerations and Data Analysis

We powered this study based on its primary Aim: intervention effects on 6-month smoking abstinence. Assuming a reference abstinence proportion of 5.8% in the smoking cessation counseling group (based on our previous bupropion trial in the CL population), using a likelihood ratio test of proportions at a significance level of 0.05, a sample size of 250 per group provides 80% power to detect a difference of 7.3% (i.e., 13.1% abstinence in the *in vivo* group, OR = 2.45).

To determine whether the abstinence rates differ over time between the two groups, a repeated measures model fitted with a generalized linear mixed-effects model or generalized estimating equations (GEE) will be used, including up to the 6-month follow-up period. This modeling approach includes a covariance structure among the repeated measurements within participants and will use all available data. If necessary, baseline covariates showing relevant baseline imbalances or associated with attrition will be included (57). Measures of effect size (e.g., Cohen's d, Cramer's V) will be used to determine baseline balance in covariates as well as the magnitude of the association between dropout and covariates. We will conduct similar analyses to evaluate differences in incidence rates of 24-h quit attempts as well as longest duration of quit attempt. To examine the secondary outcome of the project (intervention effects on medication adherence during the 10-week intervention period), we will use repeated measures modeling, as described above.

Exploratory moderation analyses will be conducted to determine whether baseline psychosocial variables such as ethnoracial identity, gender, educational attainment, and annual income, or smoking characteristics such as motivation to quit, abstinence self-efficacy, prior use of NRT, and abstinence-related expectancies moderate the relationship between intervention group and abstinence. These analyses will be conducted by fitting models with interaction terms for study group by moderator. We will also conduct mediation analyses (58, 59) to determine if factors such as medication adherence, withdrawal and craving, treatment engagement, and motivation to quit mediate the effect of intervention group on abstinence. These analyses will be conducted using path modeling to partition the intervention effect into direct and indirect. Lastly, we will examine treatment retention (% of people who were not lost to follow-up at 6-months), and engagement (# of study appointments completed) as well as therapist ratings for participants who completed study visits all in person, all remote, or a mixture of both modalities.

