## Methods and Analysis

### Study Design and Hypotheses

Participants are randomized to one of two conditions (1:1) testing four 30-min sessions delivered over 4 weeks. A blocked randomization procedure with random blocks sizes 10 and 20 was used to generate the randomization list. The *in vivo* group receives in session NRT sampling with a focus on expectancies for medication and experience using the medication in session. The counseling group receives standard smoking cessation behavioral counseling. All participants receive NRT for 13 weeks with additional nonintervention follow-ups at 1-, 3-, and 6-months post-intervention. Thus, all participants receive almost the same level of evidence-based medication (*in vivo* group receives an additional 2 weeks during sessions 1 and 2); the only differences are the process of introducing it (guided sampling vs. not) and the difference in behavioral sessions (e.g., focus on experience with medication vs. standard smoking cessation behavioral strategies). Specifically, the patch and lozenge were chosen, and the dosage and duration of use were based on standard of care practices (49, 50). These products were chosen because the patch provides a steady dose of nicotine throughout the day while the lozenge is a short-acting NRT, which can help curb cravings in the moment (51). Nicotine gum is another over-the-counter, short-acting option, however using gum requires dentation. Unlike the nicotine inhaler and nasal spray, the patch and lozenge do not require a prescription (44). All procedures are approved by the institutional review board at the University of Alabama at Birmingham (UAB). It is expected that individuals who experience the effects of the medication during sessions will have increased adherence and cessation relative to participants who receive standard smoking cessation counseling.

Importantly, sessions began in person for the first 364 participants, but were changed to primarily remote sessions as COVID-19 precautions were put in place, with 273 participants completing a combination of in-person sessions and some remote sessions. After 6/1/20, the study procedures were modified so that participants are now required to attend an in-person baseline visit with the remaining nine appointments conducted remotely. Participants complete the sessions (*in vivo* or standard counseling) over the phone with study staff and complete all study measures *via* email, text, or verbally over the phone.

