### Participants

Participants are recruited from the University of Alabama at Birmingham (UAB) Substance Abuse programs including Beacon Addiction Treatment Center (BATC), Treatment Alternatives for Safer Communities (TASC), Court Referral (CRO) Program, drug court, mental health court, community corrections, etc. with flyers posted in relevant locations and *via* snowball recruitment. Interested participants are encouraged to call or email the study team to complete eligibility screening. All study related activities are conducted by research staff only. The recruitment goal for this study is 517 smokers currently under community corrections supervision (not incarcerated). Participants who complete all study appointments receive $440 in compensation.

Potential study participants are phone screened and must be (a) under community criminal legal supervision or will be on probation or parole over the next 6 months, (b) smoking at least 5 cigarettes/day for the past year (c) 18 years of age or older, (d) able to read and speak English, (e) able to provide contact information for at least 2 people if we cannot reach the participant (f) living in an unrestricted environment that allows smoking, (g) able to access a smartphone or a personal email address. Participants must not (h) be pregnant or breastfeeding, (i) have a cognitive impairment or untreated mental illness that interferes with informed consent (based on the judgment of the research assistant if the participant is not responding appropriately or gives any indication that they are not understanding the study), (j) have experienced (within 6 months) post-myocardial infarction or untreated severe angina, (k) have a known sensitivity to NRT or adhesive products (l) exclusively use other tobacco products (e.g., cigars, e-cigarettes; although concurrent use of other tobacco products was not an exclusion criterion), or (m) be currently receiving treatment to quit smoking. It is not an eligibility requirement that participants be motivated to quit smoking. The cutoff of five cigarettes/day was chosen based on the logic that we do not want to enroll people who are light smokers or nondaily smokers for a treatment study, given that the intervention includes use of NRT. Five cigarettes/day is commonly used as a cutoff in many other smoking treatment research studies (52–54).

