An additional limitation of the present intervention could be that it is not intensive enough to promote a change in smoking behavior. A sampling intervention such as this may not provide the intensive and prolonged treatment that is necessary for a chronic relapsing condition such as smoking (66). However, time and resource-heavy interventions are unlikely to be implemented in busy clinical or low-resource settings. The proposed intervention was designed to be brief and simple enough to be implemented in busy settings by non-therapist providers but still intensive and targeted to encourage behavior change. While the PI is not a Tobacco Treatment Specialist (TTS) and the staff were not sent for specific TTS training, they are a clinical psychologist with research and clinical experience in both treating and training other clinicians about tobacco treatment,. Furthermore, RA level staff completed the counseling treatment fidelity ratings rather than a clinical supervisor or an outside clinician. Finally, as previously mentioned, intervention procedures were adapted in order to reduce staff-participant contact as the COVID-19 pandemic evolved. While necessary, these adjustments (e.g., primarily conducting remote sessions) could negatively affect the *in vivo* experience and impact the therapeutic interaction. Additionally, another potential issue in the study is the ability to retain participants until study end. Oftentimes people in the CL population have unpredictable lives, where unstable housing situations, cell phone access, transportation, etc. can impact participants' ability to adhere to the study protocol (67). Missed appointments are expected to be similar to our previous study (25–30% missed appointments at any point up to 6 months post intervention). The analytical approach will use all available data adjusted for characteristics relevantly associated with attrition, if any, and thus decreasing potential bias from missing data (57).

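### The stated 80% power requires about 250 observed 6-month outcomes per group; the 517 recruits allow for about 3% loss, while the article expects 25–30% missed appointments

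*Protocol article*

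**What the plan says.** All references are to the protocol article.

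- **Sample Size Considerations and Data Analysis.** The study is powered on 6-month abstinence. The inputs are "Assuming a reference abstinence proportion of 5.8% in the smoking cessation counseling group" (taken from the team's previous trial), "13.1% abstinence in the" in vivo group, and a test specified as "using a likelihood ratio test of proportions at a significance level of 0.05". The result is that "a sample size of 250 per group provides 80% power to detect a difference of 7.3" percentage points (OR 2.45). No allowance for loss is mentioned.
- **Study Design and Hypotheses.** "Participants are randomized to one of two conditions (1:1").
- **Participants.** "The recruitment goal for this study is 517 smokers currently under community corrections supervision (not incarcerated").
- **Limitations and Strengths.** "Missed appointments are expected to be similar to our previous study (25–30% missed appointments at any point up to 6 months post intervention"). The section then says: "The analytical approach will use all available data adjusted for characteristics relevantly associated with attrition", if there are any.
- **Outcomes.** The primary outcome is CO-confirmed 7-day point prevalence abstinence at 6 months. The section says how other tobacco use and a CO reading above the cutoff from other smoke are classified. It gives no rule for a missed visit.

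**The concern.** Four statements in the same article do not fit together: 80% power at 250 per group, 517 recruited, an expected 25–30% of missed appointments, and an analysis of available data. If 250 per group is the number needed with an outcome, 517 recruits leave almost no room for loss. If 250 per group is the number randomised, the 80% takes no account of the loss that the authors themselves expect.

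This is the article's only power statement, and it supports the primary aim. If the real power is lower, the chance of missing a true 7.3-point effect is larger than the advertised 20%. A null result could then be read as stronger evidence against such an effect than it is.

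**Working it through.** **Inputs.** Control rate p₁ = 0.058, intervention rate p₂ = 0.131, α = 0.05, likelihood ratio test (sample size section); 1:1 allocation (design section); 517 recruited (Participants); 25–30% (Limitations). Sidedness is not stated. A 1-df likelihood ratio test is two-sided, and a one-sided test of proportions would give 87.6% at 250 per group, so two-sided is the reading that matches 80%.

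**Step 1: reproduce the plan's figure.**

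- Odds ratio: (0.131/0.869) ÷ (0.058/0.942) = 2.45, as stated.
- With n per group and p̄ = (0.058 + 0.131)/2 = 0.0945, the non-centrality is λ = 2n Σᵢ [pᵢ ln(pᵢ/p̄) + (1 − pᵢ) ln((1 − pᵢ)/(1 − p̄))] = 0.03189 n.
- Power = P(χ²₁(λ) > 3.841).
- At n = 250, λ = 7.97 and power = 80.6%. A pooled z-test gives 79.9%, and exact enumeration of the likelihood ratio test gives 81.3%.

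The stated 80% is therefore correct for 250 per group with complete outcomes.

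**Step 2: the allowance built into 517.**

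- 1 − 500/517 = 3.3%.
- Solving the same formula for 80% power gives about 246 observed per group. With 517/2 = 258.5 recruited per group, that is 246/258.5 ≈ 95% with a 6-month outcome.

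**Step 3: power at different levels of month-6 missingness.** Observed n per group = 258.5 × (1 − d), comparing those observed at 6 months.

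| Missing at month 6 (d) | Observed per group | Power, 5.8% vs 13.1% |
|---|---|---|
| 0% | 258.5 | 82% |
| 5% | 246 | 80% |
| 10% | 233 | 78% |
| 15% | 220 | 75% |
| 20% | 207 | 73% |
| 25% | 194 (517 × 0.75 = 388 in all) | 70.1% |
| 30% | 181 (517 × 0.70 = 362 in all) | 67.1% |

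At 25% and 30% the pooled z-test gives 69.2% and 66.2%, and the exact likelihood ratio test gives 71.4% and 68.3%. The choice of method moves the answer by one or two points.

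**Step 4: effect detectable with 80% power, control rate held at 5.8%.**

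- 194 per group: 14.2%, a difference of 8.4 points, OR 2.69.
- 181 per group: 14.6%, a difference of 8.8 points, OR 2.77.

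**Step 5: what if missing counts as smoking?** The article does not say this, so both cases are shown.

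- If 5.8% and 13.1% are already on that basis, all 517 are analysed and power is about 81–82%.
- If 5.8% and 13.1% are rates among those observed, they shrink to 4.35% vs 9.83% (25% missing) or 4.06% vs 9.17% (30% missing). With 258.5 per group, power is 69% or 66% by the likelihood ratio formula (68% or 65% by pooled z).

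**The case against.** **The sentence is true as written.** 250 per group does give 80% power, and the sentence claims nothing about power after attrition. A reader might infer that the authors miscalculated; they did not. What remains is that the article's own recruitment goal, expected loss and analysis approach do not deliver the 250 observed per group on which the figure depends. That is a conflict between printed statements, not a detail left to an analysis plan.

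**The 25–30% is not plainly a month-6 missing rate.** It describes missed appointments at any point over a period. It could be a per-visit rate, or the share who ever miss a visit, in which case month-6 missingness would be lower. The exploratory analyses define retention separately and give no expected value. This objection stands, and 25–30% missing at month 6 must be labelled an assumption. It is still the natural reading, because the phrase follows a sentence on retaining participants to study end and leads into attrition and missing data. A milder reading shrinks the shortfall but does not remove it unless month-6 loss is about 5% or less.

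**The planned analysis is not a completers-only test.** A mixed model or GEE uses earlier visits, and smoking status and CO are scheduled at every visit. This also stands. A reader might infer that the trial's power is 67–70%; the article does not support that as a firm figure. It is the power of a 6-month comparison among those observed, and the repeated-measures model would do better. By way of illustration only, suppose everyone missing month 6 has an earlier visit correlated 0.5–0.7 with it. Power is then about 73–76% at 25% missing and 70–74% at 30%. Those correlations are not in the article, so the gain cannot be fixed, but under this illustration a shortfall remains.

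**The basis of the 5.8% is not shown.** If the previous trial counted missing as smoking and this trial does the same, about 80% stands. The article states neither, and what it does describe is an available-data analysis.

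**Conclusion.** The point holds in conditional form. The 80% is correct for about 250 observed outcomes per group and cannot be carried over to 517 recruits with the loss the article expects. Assuming 25–30% missing at month 6 and a comparison of observed outcomes, power is about 67–70%. The chance of missing a true 7.3-point effect is then about 30–33% rather than 20%, and the effect detectable with 80% power rises to about 8.4–8.8 points. At 10–20% missing, power is about 73–78%. The repeated-measures model would raise these figures by an amount the article does not allow to be computed. The one route by which about 80% survives without near-complete follow-up is a missing-equals-smoking rule applied both to the 5.8% and to the primary analysis, and no such rule is stated.

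The stated power should be corrected or its basis declared. A reader might go further and conclude that the trial must recruit more; that does not follow, since the defect is in the stated figure and can be put right there.

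**What to change.** Restate the power at the month-6 missingness actually expected, and say whether 250 per group means randomised or observed. Suggested wording: *Assuming 25–30% missing at 6 months, 517 randomised gives about 67–70% power for 5.8% versus 13.1% in a comparison of observed 6-month outcomes, and somewhat more under the repeated-measures model.* If the expected month-6 loss is a different figure, give that figure and the matching power.

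Alternatively, if the 5.8% was computed with missing counted as smoking, say so and make the same rule the primary analysis; about 80% then stands. That choice also means revising the available-data description in the analysis and limitations sections so that the two agree.

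The cost is one rewritten sentence and a less favourable stated power under the first option, or an explicit commitment on missing outcomes under the second. Neither needs extra enrolment or a change of endpoint.

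### The primary outcome and the power calculation concern 6-month abstinence, but the only abstinence analysis named asks about differences over time, and no month-6 contrast is designated as the primary test

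*Protocol article*

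**What the plan says.** All references are to the protocol article.

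- **Outcomes.** "The primary outcome variable will be smoking 7-day point prevalence abstinence confirmed by a CO" cutoff, and the time point given is the 6-month follow-up. Abstinence across the study is then listed as a further examination.
- **Sample Size Considerations and Data Analysis, first paragraph.** "We powered this study based on its primary Aim: intervention effects on 6-month smoking abstinence". The calculation starts from this premise: "Assuming a reference abstinence proportion of 5.8% in the smoking cessation counseling group". Its method is given as "using a likelihood ratio test of proportions at a significance level of 0.05". The result claimed is that "a sample size of 250 per group provides 80% power to detect a difference of 7.3" percentage points, which means 13.1% in the in vivo group and an odds ratio of 2.45.
- **Same section, second paragraph.** The abstinence analysis is introduced as "To determine whether the abstinence rates differ over time between the two groups, a repeated measures model fitted with a generalized linear mixed-effects model". An alternative fitting method and the time span follow: "or generalized estimating equations (GEE) will be used, including up to the 6-month follow-up period". The secondary outcome, medication adherence, is sent back to this same repeated-measures approach.
- **Limitations and Strengths.** The analytical approach is described as using all the data available, with adjustment for characteristics linked to attrition.

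The likelihood ratio test appears only in the power sentence. No sentence assigns a test to the 6-month outcome.

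**The concern.** The question that was powered and the question attached to the model differ. A single 6-month comparison of two proportions has one null hypothesis: equal abstinence at month 6. A repeated-measures model aimed at differences over time suggests one of two other nulls. One is no group effect averaged over visits; the other is no group-by-visit interaction. The three nulls coincide only in special cases.

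If the primary p-value came from an over-time test, a benefit that had gone by month 6 could be reported as success on the primary aim. A real 6-month benefit could equally be reported as failure. Because the text does not choose, the choice could also be made after the results are known.

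There is a smaller point about scale. GLMM and GEE are offered as alternatives, but a GLMM coefficient is a subject-specific odds ratio, whereas GEE gives a population-average one. The planned 2.45 is computed from two marginal proportions, so only the population-average scale is comparable with it.

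**Working it through.** **1. The plan's own figure.** Inputs from Sample Size Considerations and Data Analysis: p1 = 0.058, p2 = 0.131, n = 250 per group, alpha 0.05 (taken as two-sided). Allocation is 1:1 (Study Design and Hypotheses).

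- Odds ratio = (0.131/0.869) / (0.058/0.942) = 0.1507/0.0616 = 2.45.
- Mean proportion = (0.058 + 0.131)/2 = 0.0945.
- z = [0.073 × √250 − 1.96 × √(2 × 0.0945 × 0.9055)] / √(0.058 × 0.942 + 0.131 × 0.869) = (1.154 − 0.811)/0.410 = 0.84, so power = Φ(0.84) = 79.9%.
- The likelihood ratio test gives 80.6% by the noncentral chi-square and 81.3% by exact enumeration.

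The 80% is right, and it belongs to the month-6 comparison.

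**2. What an over-time test targets.** The visits are weeks 8 and 12 and months 1, 3 and 6 (Follow-Up Procedures). The article gives no abstinence rates before month 6 and no within-person correlation, so the following are assumptions.

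| Scenario | Counseling, % | In vivo, % |
|---|---|---|
| A: early effect, none at month 6 | 12, 11, 9, 7, 5.8 | 24, 21, 16, 9, 5.8 |
| B: planned month-6 effect, little before | 12, 11, 10, 8, 5.8 | 12, 11.5, 11, 11.5, 13.1 |
| C: odds ratio 2.45 at every visit | 12, 11, 9, 7, 5.8 | from the odds ratio |

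The visit-averaged effect is the mean of the five log odds ratios.

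- A: (0.840 + 0.766 + 0.655 + 0.273 + 0)/5 = 0.507, odds ratio 1.66, while the month-6 odds ratio is 1.
- B: (0 + 0.050 + 0.107 + 0.402 + 0.895)/5 = 0.291, odds ratio 1.34, while the month-6 odds ratio is 2.45.
- C: the average and the month-6 odds ratio are both 2.45, and the interaction is zero.

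**3. Rejection rates.** Simulation: 250 per group, complete data, 3000 trials per cell, binary outcomes from a correlated latent normal (AR(1) 0.7 or exchangeable 0.6). Logit marginal model with independence working correlation, saturated in group and visit, robust covariance. Ranges cover the two correlation structures.

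| Scenario | Visit-averaged | Group-by-visit (4 df) | Month-6 contrast |
|---|---|---|---|
| No difference at any visit | 5% | 5% | 4% |
| A | 72–75% | 35–50% | 3–4% |
| B | 30–33% | 45–62% | 81–82% |
| C | almost 100% | 4% | 80% |

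**4. Sensitivity to the assumptions.** A second run at 250 per group worked on the risk scale, with other assumed early-only rates (20, 20, 18, 10, 7% vs 10, 10, 9, 8, 7%). The visit-averaged test rejected 79–89%, the group-by-time test 93–97% and the month-6 contrast about 5%. With 13.1% vs 5.8% at every visit, the figures were 95–99%, 5% and 81%. The sizes move with the assumed rates, correlation and scale; the pattern does not.

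**5. Scale of the odds ratio.** Under a random-intercept logistic model, the marginal proportion is the mean of expit(β + σZ) with Z standard normal. Solving for marginal 5.8% and 13.1% gives conditional odds ratios of 3.4, 4.9 and 7.3 for σ = 2, 3 and 4. These σ values are assumptions; the article gives none.

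**The case against.** The strongest reply is that nothing conflicts. Outcomes separates the 6-month primary outcome from abstinence across the study, and the analysis section keeps that order: the primary aim with a test of proportions, then a model for change over time. On that reading the likelihood ratio test is the implied primary analysis and the model serves the further aim. This reading is possible, but the text never states it. Two statements point the other way. The secondary outcome is referred back to the repeated-measures model as the established approach. Limitations and Strengths describes covariate adjustment with all available data, which fits that model and not a two-proportion test at one visit.

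Second, the article specifies no time coding, interaction or contrast, and the model extends to the 6-month visit, so it can yield the month-6 contrast. That stands. Such detail could also sit in an analysis plan that is not shown. What remains is that the stated purpose of the model differs from the stated primary outcome.

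Third, the simulated rates rest on invented early-visit figures, and the over-time tests do not always fail: under a constant effect, the visit-averaged test is more powerful than the month-6 contrast. Both are correct. Nor does the early concentration of sessions and NRT prove that a between-group effect would fade, since the two groups share most of that schedule.

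A reader might infer that the protocol has made the over-time p-value its primary result, or that it tests the wrong quantity. The article does not support that: it never calls that p-value primary.

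**Conclusion.** The point holds as a mismatch between the stated primary outcome and the stated purpose of the only abstinence model. It is not a demonstrated error in the primary test. The sample size calculation is sound for the month-6 comparison, and the named model can deliver that comparison.

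The stakes are material because the candidate tests behave so differently. With equal month-6 rates, an over-time test rejected in roughly one third to nearly all simulated trials, depending on the test and the assumed rates, against 3–5% for the month-6 contrast. With the planned month-6 effect, power ranged from about 4% (group-by-time, constant effect) to almost 100% (visit-averaged, constant effect), against 80–82% for the month-6 contrast. These figures are illustrations resting on assumed early rates, assumed correlations and complete data.

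The choice between GLMM and GEE is a lesser matter of reporting scale. The article does not commit to reporting on the scale of the 2.45, but a GLMM coefficient should not be set beside that figure.

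**What to change.** State in the analysis section that the primary test is the group difference in CO-verified 7-day abstinence at the 6-month visit. Take it as the month-6 contrast from the repeated-measures model already planned, with visit as a categorical factor and group-by-visit terms. The powered two-proportion test at month 6 is an acceptable alternative; name one of the two. Make the visit-averaged and group-by-time tests secondary.

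Report the primary result on the population-average scale, as a risk difference and a marginal odds ratio, from GEE or from a GLMM standardised to marginal proportions.

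The cost is a few sentences of analysis wording, with no new data or visits, to be settled before outcomes are compared by group. In the simulations of step 3, the month-6 contrast kept 80–82% power at 5.8% vs 13.1% and rejected in 3.3–4.1% of trials when month-6 rates were equal. The stated 80% power then applies to the test actually used, before allowing for missed visits.
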